### Secondary objectives

The secondary objectives are as follows:To estimate and model the likely effectiveness and cost effectiveness of MiQuit compared with usual care including a generic smoking cessation information leaflet.To document participants’ use of MiQuit interactive features and of NHS cessation support.To assess the effect of MiQuit on social cognitive determinants of quitting smoking.To explore participant views and experiences of using MiQuit.To explore research staff views and experiences of the MiQuit pilot trial.

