### Other outcomes

Other outcomes include the following:Use of NHS cessation support.Social cognitive variables such as health beliefs and outcome expectancies.Process variables such as number of contacts with MiQuit for tailoring of content and increase or decrease requests.

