**Table 1 Tab1:** **Participant assessments at each time point**

**Participants Assessments**	**Pre-screen**	**Visit 1: Baseline**	**Randomisation**	**Visit 2: 4 week Follow-up**	**Visit 3: Late Pregnancy/Postnatal Follow-up**	**Visit 4: Validation of smoking status**
Trial Unit (PS)	**X**					
Acute Unit (PS)	**X**					
Consent^a,b^	**X**					**X**
Visit Dates^c^		**X**		**X**	**X**	**X**
Demographics/Education		**X**				
Smoking Behaviour 1		**X**				
Smoking Behaviour 2		**X**				
Smoking Behaviour 3						**X**
Smoking Beliefs		**X**			**X**	
Pregnancy		**X**				
Relationship Status		**X**				
Eligibility Criteria Check		**X**				
EQ-5D-3 L^d^		**X**		**X**	**X**	
Allocation - MiQuit/Control			**X**			
Abstinence Check				**X**		
Stop Smoking Strategy/Quit attempts					**X**	
Attitude to Intervention (MiQuit only)^e^					**X**	
Assessment of Tobacco Exposure^f^						**X**

^a^Telephone and written consent will be performed at Pre-screening.

^b^Written consent for cotinine sample collection will be performed at V4 for those who provided telephone consent at pre-screening.

^c^Telephone/face to face visit will be performed at V1 (only) and face to face/postal visit will be performed at V4 (only). Visits 2 and 3 will be telephone, with questionnaires sent to any who cannot be contacted.

^d^EQ-5D-3 L - European Quality of life Five Dimension, Three Levels questionnaire to be completed by the participant.

^e^A small number of those who are allocated to the MiQuit group and consent at baseline will be contacted for a qualitative telephone interview to provide feedback on their experience of the study and intervention.

^f^Measured with saliva cotinine and/or exhaled CO levels.

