**Participant flowchart: study design and the timeframe for follow-up assessments.**

### Visit 1 - baseline

After giving informed consent, participants will be asked to complete a baseline questionnaire, which may be over the telephone with the study team member (*recruitment method one*) or over the telephone with a local RM or in person by the RM (*recruitment method two*). This will confirm contact details and ask about socio- demographic data, smoking attitudes and behaviour (for MiQuit tailoring), heaviness of smoking [15], gestational age, number of births beyond 24 weeks, partner’s (significant other’s) smoking status and health status (EQ-5D) [16].

The researcher will enter the participant details on the electronic database and then randomise the participant. This will ensure the researcher will remain blinded to the participant allocation. The participants are randomised, using the Nottingham Clinical Trials Unit's web-based service, to intervention (MiQuit) or control. For participants in either trial arm, a specific information sheet, which describes only details of procedures employed within that arm, will be generated and sent to them by a non-blinded member of the trial team who is not involved in follow-up. Documentation will also include a leaflet giving some information and advice on stopping smoking, details of a contact point for participants who have questions about trial involvement and details of how participants can reverse their decision to take part (outlined in - removal of participants from intervention or assessments). The PIS, information sheets and consent form will be available in English only, as understanding of English is required to receive the MiQuit intervention.

Follow-up contacts will use a blend of postal, telephone, email/web and SMS text messaging reminders to elicit maximal response rates. For those participants reporting a quit, where possible, a home visit from their local RM will be arranged.

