### Visit 3 - late pregnancy/postnatal follow-up

*At 36 weeks gestation*: Participants will be asked to complete a questionnaire (data to be collected up to 10 weeks after estimated delivery date will be acceptable for use). This will include quality of life information (EQ-5D) and measures of smoking behaviour, attitudinal/behavioural information, use of NHS smoking cessation support and participants’ ratings of the intervention (MiQuit arm only). As for the 4-week visit, this visit will be performed mainly via telephone by a member of the study team at the co-ordinating centre, blind to treatment allocation. As for the 4-week visit, previously-described alternative methods will be employed to elicit the best response rate.

It is recognised that asking about the intervention at follow-up will result in the researcher who conducts the late pregnancy follow-up becoming un-blinded. To ensure that this has minimal impact on follow-up data obtained, the participants will be asked items about the intervention at the end of the interview/questionnaire starting with the question ‘*Did you receive any stop smoking text messages from the study team*?’

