These variables have been chosen as potentially requiring adjustment because, in previous studies, they have been shown to be associated with smoking cessation in pregnancy [20,21].

Other smoking outcomes will be analysed using similar methods: 95% confidence intervals will be presented along with exact two-sided *P* values. Descriptive analyses will be performed to assess the effect of the intervention on the use of NHS cessation support, use of interactive features of the intervention and social cognitive variables.

We also plan to explore the mechanism of effect for the MiQuit intervention that is, how the intervention might change smoking behaviour. For this, we will undertake mediation analyses to explore whether potential changes in social cognitive determinants of smoking cessation explain changes in quitting behaviour. This will be a secondary analysis and, therefore, covered in a separate paper rather than in the main trial outcomes paper.

Health economic analysis will investigate the potential incremental cost-effectiveness of MiQuit using costs (actual and estimated) of delivering the intervention and estimates for its effectiveness derived from the trial. Models developed in previous studies will be used to project the likely cessation rates into longer term estimates of life years gained.

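### The effect of MiQuit on smoking beliefs is a secondary objective, but the only method stated for it is descriptive, with no between-group estimate, confidence interval or use of the baseline score

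*Protocol article*

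**What the plan says.** All references are to the protocol article.

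- **Secondary objectives**, third item: "To assess the effect of MiQuit on social cognitive determinants of quitting smoking". This is a question about the difference between the randomised groups.
- **Other outcomes** lists "Social cognitive variables such as health beliefs and outcome expectancies".
- **Table 1** has a row "Smoking Beliefs", marked at visit 1 (baseline) and visit 3 (late pregnancy/postnatal). The row is not limited to one arm, whereas the row on attitude to the intervention is marked as MiQuit only.
- **Visit 1 - baseline** confirms collection of "smoking attitudes and behaviour (for MiQuit tailoring"). **Visit 3** confirms "measures of smoking behaviour, attitudinal/behavioural information, use of NHS smoking cessation support".
- **Data analysis** gives the method: "Descriptive analyses will be performed to assess the effect of the intervention on the use of NHS cessation support, use of interactive features", and the same sentence ends with the social cognitive variables. The sentence just before it, on confidence intervals and P values, covers the other smoking outcomes only. The logistic models adjusted for centre and gestation are also for smoking outcomes.
- The same section adds that "we will undertake mediation analyses to explore whether potential changes in social cognitive determinants of smoking cessation explain changes in quitting behaviour", to be "covered in a separate paper rather than in the main trial outcomes paper".

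**The concern.** The objective is causal, the comparison is randomised and a baseline measure exists, yet the stated method is description. One sentence gives the same treatment to three kinds of variable. Use of interactive features exists only in the MiQuit arm, so description is all that is possible there. Beliefs are measured in both arms, so an effect can be estimated.

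At stake is how well this objective is answered. The Background reports that the earlier feasibility trial found effects on harm beliefs, confidence and determination to quit. Summaries by arm, with no difference and no interval, would not show how large such an effect is here or how uncertain it is. If the baseline score is also left out, a chance baseline difference between the arms stays in the apparent effect and the comparison is less precise than the data allow. No sample size, significance level or decision rule in the article depends on the belief scores.

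**Working it through.** **1. The plan's own figures.** The article gives no precision figure for beliefs. Its nearest figures are the margins of error for quit rates, which reproduce at a 10% rate:
- both groups, n = 400: 1.96 × sqrt(0.10 × 0.90 / 400) = 2.94%, stated as 3%;
- one group, n = 200: 1.96 × sqrt(0.10 × 0.90 / 200) = 4.16%, stated as 4%.

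The odds-ratio intervals in Tables 2 to 5 reproduce to within 0.01 (for example 0.82 to 2.76 for an odds ratio of 1.5 at a 10% control rate). The article therefore plans intervals for other secondary effects, and its arithmetic there is sound.

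**2. Inputs for beliefs.** From the article: 400 women, 1:1, so 200 per arm. Not in the article, so assumed:
- the correlation rho between baseline and visit 3 score, taken as 0.3 to 0.7;
- roughly continuous scores with equal SD at both times (results are in SD units);
- the same items at both visits, as the shared row in Table 1 suggests.

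**3. Formulas.** For n per arm, the variance of the between-group difference in SD units is:
- visit 3 score alone: 2/n;
- raw change from baseline: 2/n × 2(1 − rho);
- adjusted for baseline score: 2/n × (1 − rho²).

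The 95% half-width is 1.96 times the square root. At n = 200, visit 3 alone gives 1.96 × sqrt(2/200) = 0.196 SD.

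**4. Results at 200 per arm.**

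| rho | Variance cut by adjustment (rho²) | Half-width, visit 3 alone | Half-width, raw change | Half-width, baseline-adjusted |
|---|---|---|---|---|
| 0.3 | 9% | 0.196 | 0.232 | 0.187 |
| 0.5 | 25% | 0.196 | 0.196 | 0.170 |
| 0.7 | 49% | 0.196 | 0.152 | 0.140 |

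**5. Fewer completers.** If 120 per arm give a visit 3 score (assumed), 1.96 × sqrt(2/120) = 0.253 SD falls to 0.241, 0.219 and 0.181 SD at rho 0.3, 0.5 and 0.7. The proportional gain is unchanged because it depends on rho alone.

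**6. Reading.** Adjustment is never less precise than the other two under these formulas. At rho 0.3 it narrows the interval by under 5% (0.187/0.196 = 0.954), and at 0.7 by about 29% (0.140/0.196 = 0.714). Raw change is worse than ignoring baseline when rho is below 0.5.

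**The case against.** **The analysis plan may settle it.** A full statistical analysis plan is to be agreed before analysis, and choosing covariates is commonly left to it. That would answer a complaint about silence. Here the article states a method for assessing this effect, and that method is descriptive. A later plan that modelled the scores would depart from it.

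**It is a feasibility pilot.** There is no single primary outcome and the analyses mainly serve feasibility. This stands against hypothesis tests, and against arguing from power, for an exploratory outcome. It does not stand against an estimate with an interval, which the article already plans for other secondary effects.

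**Mediation uses these data.** A reader might infer that no analysis anywhere will use the baseline beliefs. The article does not support that. The mediation analysis works on changes in these variables, its mechanism analysis is assigned to the intention-to-treat population, and such work ordinarily needs the effect of allocation on the mediator. But it asks whether belief changes explain quitting, is reported elsewhere, and states no baseline-adjusted difference.

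**More can be read in than is written.** A reader might infer that the main paper will show visit 3 summaries only, with baseline ignored. The article does not say so; descriptive analysis could include baseline values or changes. Nor can one infer bias: under randomisation an unadjusted comparison is unbiased. The baseline items also have another stated purpose, tailoring the messages.

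**The size is assumed.** This stands. Entry is before 25 weeks and visit 3 is at 36 weeks or later, a gap of more than 11 weeks, so a low rho is plausible. If the measures are single ordinal items, the variance formula is only a guide.

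**Conclusion.** The point holds in a limited form. The article sets an effect on social cognitive determinants as a secondary objective and collects beliefs at two times in both arms. The only method it states for that effect is descriptive, with no between-group estimate, interval or use of baseline. That gap does not depend on any assumed value.

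The added gain from baseline adjustment does depend on one. Variance falls by 9% to 49% for an assumed rho of 0.3 to 0.7, and at 200 per arm the half-width falls from 0.196 SD to 0.187 to 0.140 SD. At the low end this is minor.

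This is a worthwhile, inexpensive improvement to an exploratory analysis. It is not an error that threatens the trial's feasibility aims or its smoking outcomes.

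**What to change.** In the Data analysis section, or in the statistical analysis plan with a note that it replaces the descriptive-only statement, add for the social cognitive variables:

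*For each belief score, the visit 3 difference between groups will be estimated with a 95% confidence interval from a linear model on allocated group, baseline score, centre and gestation stratum (<16 v ≥16 weeks), in women with a visit 3 score. Single ordinal items will use an ordinal model with the same terms. These are exploratory estimates without hypothesis tests, shown beside descriptive summaries by arm.*

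Centre and gestation are the stratification factors already used in the smoking models, so the two sets of analyses match. Keep descriptive analysis for use of interactive features.

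The cost is that sentence and a few regressions on data already being collected, with no change to design or sample size. The small downside is a handful of extra exploratory estimates, which the label is meant to keep in proportion.

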### Visit 2 - 4-week follow-up

*At 4 weeks after randomisation*, participants will be contacted via telephone in order to assess smoking status, numbers of quit attempts lasting more than 24 hours, quality of life information (EQ-5D) and use of NHS and non-NHS smoking cessation support in the period since randomisation. This visit will, in general, be performed via telephone by a member of the study team at the co-ordinating centre, blind to treatment allocation; however, should the study team be unable to contact by the participant by telephone, other methods will be used in an attempt to elicit the best response. These include; posting a short questionnaire with explanatory letter and pre-paid return envelope, or sending a link, which allows web-based completion or by text.

It is possible that if members of the co-ordinating centre study team speak to participants at the 4-week follow-up, they may become un-blinded for the late pregnancy follow-up (visit 3). However, the value of exploring the feasibility of different follow-up approaches for this pilot trial outweighs the small risk of bias presented by this scenario.

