### Definition of populations analysed

For the efficacy and cost-effectiveness estimate assessments, all randomised participants will be used in the analyses using intention-to-treat population as defined below. All participants in the intention-to-treat population will be used for establishing use of NHS smoking cessation support and for the mechanism of effect analysis.

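### Smoking beliefs are re-measured only at visit 3, after the qualifying quit began, so the planned mediation analysis can show association but cannot establish mediation

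*Protocol article*

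**What the plan says.** Secondary objective 3 in the protocol article is "To assess the effect of MiQuit on social cognitive determinants of quitting smoking". The Other outcomes section lists "Social cognitive variables such as health beliefs and outcome expectancies". Two analyses use these variables, both in the Data analysis section:

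- **Descriptive.** "Descriptive analyses will be performed to assess the effect of the intervention on the use of NHS cessation support, use of interactive features"; the sentence goes on to include the social cognitive variables.
- **Mechanism.** "we will undertake mediation analyses to explore whether potential changes in social cognitive determinants of smoking cessation explain changes in quitting behaviour". The article calls this a secondary analysis and assigns it to a separate paper. The section defining the analysis populations adds: "All participants in the intention-to-treat population will be used for establishing use of NHS smoking cessation support and for the mechanism of effect analysis".

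On timing, the Table 1 row "Smoking Beliefs" is marked under visit 1 and visit 3 and nowhere else. The visit texts agree. The 4-week contact is made "in order to assess smoking status, numbers of quit attempts lasting more than 24 hours, quality of life information (EQ-5D) and use of NHS"; the list closes with other cessation support and has no belief items. Visit 3 collects "measures of smoking behaviour, attitudinal/behavioural information, use of NHS smoking cessation support and participants’ ratings of the intervention (MiQuit arm only" in one questionnaire. Under Smoking outcomes, the continuous-abstinence measure takes the quit attempt to start within 4 weeks of randomisation.

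**The concern.** A mediation claim needs the mediator to be measured after the intervention has acted and before the outcome occurs. Here the only post-baseline belief score comes after the 4-week outcome and alongside the late-pregnancy one. A woman who has stopped smoking may well come to think differently about smoking because she has stopped. If so, beliefs and quitting are correlated at visit 3 even when MiQuit did nothing through beliefs.

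This matters for later design decisions more than for the pilot's main results. The Background section gives earlier effects on harm beliefs, confidence and determination as part of the case for MiQuit. A mechanism paper that reads reverse causation as mediation could influence changes to the messages, and the same visit schedule could be carried into the definitive trial.

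**Working it through.** **1. Order of measurement (from Table 1, the visit texts and Smoking outcomes)**

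| Event | Time |
|---|---|
| Beliefs, first measure | Baseline |
| Start of qualifying quit | Within 4 weeks of randomisation |
| 4-week outcome | 4 weeks after randomisation |
| Beliefs, second measure | Visit 3: 36 weeks gestation, accepted up to 10 weeks after the estimated delivery date |
| Late-pregnancy smoking report | Visit 3, same questionnaire |
| Biochemical validation | Visit 4, only for quits already reported at visit 3 |

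Women enter before 25 weeks. The latest qualifying quit therefore starts before 25 + 4 = 29 weeks, more than 36 − 29 = 7 weeks before visit 3. In the stratum below 16 weeks the gap exceeds 36 − 16 − 4 = 16 weeks. Belief measures in both arms between randomisation and either outcome: none. Late-pregnancy point prevalence has the same problem, because it is reported together with the beliefs.

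**2. Size of the artefact when true mediation is zero**

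The plan gives no figure to reproduce. Inputs from the plan: 200 per arm, control quit rate 10%, odds ratio 1.8 (both within the ranges of its precision tables). Assumptions of this check: baseline and follow-up beliefs correlate at r = 0.5, so residual variance is 1 − 0.25 = 0.75; quitting shifts beliefs by d = 0.5, 0.8 or 1.0 SD; the intervention has no other route to beliefs.

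- MiQuit quit odds: 1.8 × 0.10/0.90 = 0.20, so the rate is 0.20/1.20 = 16.7% and the difference is 0.067. Total effect: ln 1.8 = 0.588.
- Apparent effect of arm on beliefs: a = d × 0.067.
- Apparent effect of beliefs on log odds of quitting: b = d/0.75.
- Apparent share mediated: a × b/0.588.
- Within-arm variance of quitting, averaged over arms: (0.10 × 0.90 + 0.167 × 0.833)/2 = 0.114.
- Standard error of a: √(0.75 + 0.114d²) × √(2/200).
- Chance that a is significant at two-sided 5%: P(Z > 1.96 − a/SE) + P(Z < −1.96 − a/SE).

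| d | a | b | Share | SE of a | a/SE | Chance a is significant |
|---|---|---|---|---|---|---|
| 0.5 | 0.033 | 0.67 | 3.8% | 0.088 | 0.38 | 6.6% |
| 0.8 | 0.053 | 1.07 | 9.7% | 0.091 | 0.59 | 9.0% |
| 1.0 | 0.067 | 1.33 | 15.1% | 0.093 | 0.72 | 11.1% |

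A simulation of 400 women (2,000 replicates per d) gave mean b of 0.68, 1.09 and 1.38. The b path was significant in 97% or more of trials. Both paths were significant in 8%, 9% and 11%. So the belief–quitting path will almost always look strong, while a formal indirect effect seldom will.

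**3. Reach of a belief measure added now**

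Trial status reports 385 women recruited from 18 February to 27 August 2014, which is 190 days, or 2.03 per day. If 4-week calls had included beliefs from that last date, about 2.03 × 28 = 57 recent recruits plus the remaining 15 would have been reached: 72 of 400, or 18%. Any delay in approval lowers this.

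**The case against.** The strongest reply is that this is an exploratory analysis in a feasibility pilot, destined for a separate paper, and that no feasibility parameter, smoking outcome or cost-effectiveness estimate depends on it. Participant interviews will also inform how the intervention is refined. All of this stands, and it limits the weight of the point. It does not remove it: an analysis plan can choose a model, but it cannot supply a measurement the schedule lacks.

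Three stronger readings are tempting and are not supported.

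- *A reader might infer that the trial would report mediation that does not exist.* The estimate is biased if quitting shifts beliefs, but on these assumptions a significant indirect effect appears in only about 7% to 11% of trials, not far above the nominal 5%.
- *A reader might infer that adding beliefs to the 4-week call would cure the problem.* That measure would coincide with the 4-week outcome, would usually still follow the start of the qualifying quit, and would reach few women.
- *A reader might infer that using the intention-to-treat population for the mechanism analysis is itself an error.* The article sets missing smoking outcomes to smoking and gives no rule for missing beliefs. Such a rule is ordinary analysis-plan content. It needs a clarifying sentence and is not a separate fault.

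It can also be said that any mediation model estimates the arm effect on beliefs, so objective 3 would not go without an estimate. That is likely, but the analysis the article names for these variables is descriptive.

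That the Smoking Beliefs row is the proposed mediator set is an inference, though the Other outcomes and Visit 3 texts support it.

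**Conclusion.** The limitation is real and fixed by the visit schedule: beliefs at visit 3 cannot be placed before quitting, so the analysis cannot separate cause from consequence. With no true mediation, a 10% control rate, an odds ratio of 1.8, r = 0.5 and a 0.5 to 1.0 SD shift, the belief coefficient is about 0.7 to 1.4 log odds per unit and about 4% to 15% of the effect appears mediated. The shift and r are assumptions, not figures from the article. The consequence is a misleading interpretation in a secondary paper. The trial's feasibility conclusions do not depend on it.

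**What to change.** 1. In Data analysis, describe the visit 3 belief–quitting analysis as exploratory association that cannot establish mediation. Base it on women with observed visit 3 beliefs, so that a missing belief score is not paired with an assumed smoking outcome, and reconcile the population statement accordingly.
2. For secondary objective 3, replace the purely descriptive analysis with the between-arm difference in visit 3 belief scores by ANCOVA, adjusted for baseline score, centre and gestation stratum, with a 95% CI. With all 400 women observed, the half-width is about 1.96 × √(1 − r²) × √(2/200): 0.17 SD at an assumed r = 0.5, 0.19 at r = 0.3 and 0.14 at r = 0.7, against 0.20 unadjusted. Loss to follow-up widens it.
3. Record an earlier belief measure, timed to precede quitting as far as possible, as a recommendation for the definitive trial.

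Items 1 and 2 need no new data. The cost is a weaker mechanism claim and a little more analysis work.
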